# 1. Protocol Summary

Full Title: Reducing OBesity Using Social Ties (ROBUST): Randomized Controlled Trial Short Title: ROBUST- RCT

Clinical Phase: III

Principal Investigator: [name], MS

**Study Description:** Randomized controlled trial comparing two behavioral weight-loss interventions; a social-network enhanced lifestyle intervention (Intervention group) and an individual level lifestyle intervention (Control group), among Black and Hispanic adults with obesity over the course of 24 weeks. This study aims to test the feasibility and acceptability reforming interpersonal barriers and addressing social network barriers to behavior change, by engaging social network members in a lifestyle intervention for weight loss compared to the lifestyle intervention alone.

**Sample Size:** *N=* *66 (Intervention index participants)*

*N=132 (Intervention Social Network members)*

*N= 66 (Control participants)*

*N=264 (Total Sample Size)*

**Enrollment:** In the intervention group, this study will enroll 66 index participants and 132 social network member subjects. In the control group, this study will enroll up to 66 index participants.

**Study Population:** Individuals who self-identify as Non-Hispanic Black or Hispanic adults 18 years of age or older with a calculated BMI ≥ 30 kg/m2

**Enrollment Period:** *24 weeks*

**Study Design:** Randomized controlled trial comparing a social-network enhanced lifestyle (intervention group) to an individual-level lifestyle intervention (control group). Subjects in both arms (n=66 each) will receive the same number of behavioral coaching sessions (15 total) with four sessions conducted in person (baseline, week 8, week 16, and week 24), and the remaining 11 sessions conducted virtually. Subjects randomized to the social network intervention will nominate up to a maximum of two members of their social network (n=132) who will also be consented at baseline, complete a brief baseline interview, and attend the virtual coaching sessions with the randomized subject at weeks 3, 5, and 15. The social network members will also complete a close-out study interview at week 24.

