## 4.2 Inclusion Criteria Index Participant

1. Black race or Hispanic ethnicity

2. Male or Female 18 years of age or older

3. Calculated BMI > 30kg/m^2^ from objectively measured height and weight by study staff

4. Access & willingness to use program food intake app via home computer or a smartphone

5. Ability to identify at least one adult social network member who will participate in the study

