## 7.1 Study Intervention Description

The study intervention is a social network intervention which consists of the involvement of participants social network members. Study participants will complete 3 communication skills sessions with their social network members which will involve the creation and utilization of positive affirmations and strategies that social network members will use to reduce undermining participants during their weight loss journey.

- Communication Skills session outline: See Appendix

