### **7.7.1 Dosing Delays/Dose Modifications**

**Not applicable**

## 7.8 General Concomitant Medication and Supportive Care Guidelines

**Not applicable**

## 7.9 Duration of Therapy and Criteria for Removal from Study

All control and treatment group participants will receive the study intervention for 24 weeks. A subject’s follow-up in the study will end after one of the following applies:

- Subject’s voluntary withdrawal
- Subject lost to follow-up
- Adverse medical event in which the participant has been advised to halt all physical activity or needs to initiate a new medically prescribed diet
- Subject death
- Completion of all scheduled study follow-up appointments

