## 8.2 Participant Discontinuation/Withdrawal from the Study

Participants are free to withdraw from participation in the study at any time upon request.

An investigator may discontinue or withdraw a participant from the study for the following reasons:

- Pregnancy
- Significant study intervention non-compliance
- If any clinical adverse event (AE), laboratory abnormality, or other medical condition or situation occurs such that continued participation in the study would not be in the best interest of the participant
- Disease progression which requires discontinuation of the study intervention
- If the participant meets an exclusion criterion (either newly developed or not previously recognized) that precludes further study participation
- Participant lost to follow-up after several attempts to contact subject to schedule study visit.

The reason for participant discontinuation or withdrawal from the study will be recorded on the Withdrawal Case Report Form (CRF). Subjects who sign the informed consent form and are randomized but do not receive the study intervention will be replaced. Subjects who sign the informed consent form, and are randomized and receive the study intervention, and subsequently withdraw, or are withdrawn or discontinued from the study, will not be replaced.

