## 12.1 Study Design/Endpoints

This randomized controlled trial will use the following primary endpoints as the promising range to justify further testing of this agent:

- At least 75% attendance rate for the participant and their network members in their respective behavioral coaching sessions.
- 80% of participants or more to have at least one network member engage in the study.
- 85% of participants and their network members or more to complete the final study assessment.

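### Replacing randomised participants who do not receive the intervention can bias the 80% engagement and 75% attendance criteria upward, and the protocol uses that trigger in two conflicting senses

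*Protocol*

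**What the plan says.** Protocol section 8.2 sets the rule: "Subjects who sign the informed consent form and are randomized but do not receive the study intervention will be replaced". It does not extend to people who received the intervention "and subsequently withdraw, or are withdrawn or discontinued from the study, will not be replaced".

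Two sections give the term different meanings:

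- Section 7.1: "The study intervention is a social network intervention which consists of the involvement of participants social network members".
- Section 7.9: "All control and treatment group participants will receive the study intervention for 24 weeks".

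Section 12.1 lists the results that would justify further testing. Two matter here: "80% of participants or more to have at least one network member engage in the study" and "At least 75% attendance rate for the participant and their network members in their respective behavioral coaching sessions". The third is 85% completion of the final assessment.

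Other text bears on the denominators. The Protocol Summary fixes the intervention arm at 66 index participants. Section 12.4.1 defines retention among people who completed the baseline assessment. Section 12.6.2 limits response evaluation to those with at least one coaching session after randomisation and calls this intent-to-treat. No section says whether a replaced participant stays in or leaves the engagement and attendance denominators.

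**The concern.** In a feasibility trial, a participant who is randomised and then never takes up the intervention is part of the result. Filling that place with someone else, and reporting on the 66 places filled, makes the rate conditional on having started. Engagement and attendance then look better than they are among the people randomised, and these thresholds decide whether the intervention goes forward.

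The size of the problem depends on which meaning of study intervention governs section 8.2. Under section 7.1, a participant whose network members never take part has not received the intervention and would be replaced, so the rule would remove the engagement failures themselves. Under section 7.9, only participants who start nothing are replaced. The bias is then smaller, but it runs in the same direction.

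**Working it through.** **The plan's own figures.** The protocol gives no calculation for the feasibility criteria or for the number replaced. Its only related figure is 98% power for an 8-pound difference (SD 10.4) with 132 participants and 15% attrition. With 66 × 0.85 = 56.1 per arm and two-sided alpha 0.05 (assumed, since it is not stated), this reproduces at 98.3%. It does not bear on this point.

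**Inputs from the protocol.** Intervention arm 66 (Protocol Summary); engagement threshold 80% and attendance threshold 75% (section 12.1). Engagement is counted in the intervention arm, because controls have no participating network members. The smallest passing count is 0.80 × 66 = 52.8, rounded up to 53.

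**Assumptions.** The number replaced (k), the share replaced (f) and the true engagement rate (p) are not in the protocol, so ranges are shown. Every replaced participant is taken to be an engagement failure.

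**Step 1: a bare engagement pass, with the replaced counted back in.** Rate = 53/(66 + k).

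| k | Rate | At least 80%? |
|---|---|---|
| 0 | 53/66 = 80.3% | yes |
| 1 | 53/67 = 79.1% | no |
| 5 | 53/71 = 74.6% | no |
| 10 | 53/76 = 69.7% | no |

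**Step 2: chance of passing if the replaced are dropped.** With true engagement p among all randomised, the rate among those kept is p/(1 − f). The chance of passing is P(X ≥ 53) for X binomial with n = 66 and that rate. The number randomised to fill 66 places is 66/(1 − f).

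| f | Randomised to fill 66 | p = 70%: rate kept | Chance of passing | p = 75%: rate kept | Chance of passing |
|---|---|---|---|---|---|
| 0 | 66.0 | 70.0% | 4.1% | 75.0% | 19.9% |
| 5% | 69.5 | 73.7% | 13.9% | 78.9% | 46.4% |
| 10% | 73.3 | 77.8% | 37.4% | 83.3% | 79.9% |
| 15% | 77.6 | 82.4% | 73.3% | 88.2% | 98.0% |

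Both true rates are below the 80% target, so every pass in this table is a wrong one.

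**Step 3: attendance.** Take the criterion as mean attendance and suppose the 66 kept average exactly 75%. Scoring the replaced as zero, the mean over all randomised is 0.75 × 66/(66 + k): 49.5/67 = 73.9% at k = 1 and 49.5/71 = 69.7% at k = 5. Zero fits people who start nothing. If the baseline visit counts as one of the 15 sessions, each non-starter scores 1/15, and the k = 5 figure becomes (49.5 + 5/15)/71 = 70.2%, still a fail.

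**Step 4: completion.** Section 12.4.1 puts baseline completers in the retention denominator, and section 7.11 places randomisation after the baseline network interview. A replaced participant has therefore normally completed baseline and still counts.

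**The case against.** The strongest reply is that section 8.2 says replaced, not excluded. It is an enrolment rule; exact denominators are commonly left to the statistical analysis plan, which is not at hand and may keep everyone randomised. That stands: removal from the denominators is an inference. It is a reasonable one, because the arm is fixed at 66, section 12.6.2 evaluates only people with a coaching session after randomisation, and nothing keeps the replaced in. The replacement rule itself is protocol text that acts during enrolment.

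The second reply is that section 7.9 gives the intended meaning. Section 8.1 speaks of the social network intervention when it means the network component, and the section 7.1 meaning taken literally would have every control replaced. The first joint session is in week 3, after coaching in weeks 1 and 2, so many participants whose members never appear will already have started; under section 7.9 they are not replaced and still count as failures. This also stands, and it limits the size of the effect.

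A reader might go further in four ways that the documents do not support:

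- That reported engagement must approach 100%, or that the rule falls on one arm only. Both need the section 7.1 meaning, which section 7.9 contradicts.
- That all failures are removed. People who start and then withdraw are not replaced.
- That the 85% completion criterion is inflated in the same way. The section 12.4.1 denominator largely prevents this.
- That the eligibility criterion "Ability to identify at least one adult social network member who will participate in the study" is a second flaw. It applies to both arms before randomisation and defines the target population, and naming a member is not the same as that member engaging.

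**Conclusion.** The point holds for engagement and attendance, conditionally. If replaced participants leave the denominators, both rates are biased upward. One replacement is enough to turn a true bare miss on engagement into a reported pass. With 10% replaced and dropped, the chance of wrongly passing at a true 70% goes from 4.1% to 37.4%. These sizes rest on assumed true rates and non-starter shares, for which the protocol gives no values. Under the section 7.9 meaning, f is the share who start nothing and may be small. Under the section 7.1 meaning, it also takes in participants whose members never take part.

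The conflict between sections 7.1 and 7.9 holds without any assumption: the trigger for replacement cannot be applied consistently as written.

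**What to change.** Preferred: delete the replacement sentence in section 8.2.

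If replacement is kept:

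1. Reconcile sections 7.1 and 7.9, and state what receiving the study intervention means in each arm for the purpose of section 8.2.
2. State in section 12.1 or 12.4.1 that every randomised index participant, including anyone replaced, stays in the engagement and attendance denominators, with non-starters counted as not engaged and as zero attendance.
3. State that replaced participants also stay in the retention denominator, which confirms what section 12.4.1 already implies.
4. Report the number replaced by arm.

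The cost is one deleted sentence, or a few lines of text and one extra tabulation. The reported feasibility rates become slightly less favourable and, if replacement is dropped, a few allocated places may go untreated.

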## 8.3 Lost to Follow Up

A participant will be considered lost to follow-up if he or she fails to return for 3 scheduled visits and is unable to be contacted by the study site staff.

The following actions must be taken if a participant fails to return to the clinic for a required study visit:

- The site will attempt to contact the participant and reschedule the missed visit within 2 days and counsel the participant on the importance of maintaining the assigned visit schedule and ascertain if the participant wishes to and/or should continue in the study.
- Before a participant is deemed lost to follow-up, the investigator or designee will make every effort to regain contact with the participant (where possible, 3 telephone calls and, if necessary, a certified letter to the participant’s last known mailing address or local equivalent methods). These contact attempts should be documented in the participant’s medical record or study file.
- Should the participant continue to be unreachable, he or she will be considered to have withdrawn from the study with a primary reason of lost to follow-up.

# 9. Correlative/Special Studies

**Not applicable**

## 9.1 Laboratory Correlative Studies

**Not applicable**

**9.1.1 Title – Laboratory Correlative Study #1 - Not applicable**

**9.1.1.1 Collection of Specimen(s) - Not applicable**

**9.1.1.2 Handling of Specimen(s) - Not applicable**

**9.1.1.3 Shipping of Specimen(s) (if multicenter) - Not applicable**

**9.1.1.4 Site(s) Performing Correlative Study (if multicenter) - Not applicable**

## 9.2 Special Studies

**Not applicable**

**9.2.1 Title – Special Correlative Study #1 - Not applicable**

**9.2.1.1 Assessment - Not applicable**

**9.2.1.2 Method of Assessment - Not applicable**

**9.2.1.3 Timing of Assessment - Not applicable**

# 10. Measurement of Effect

## 10.1 Response Criteria

To assess the primary objective, feasibility will be assessed based on rates of recruitment, study conduct (intervention and enactment fidelity), retention and acceptability of the study. Descriptive statistics will be used to summarize recruitment rates. The screening-to-enrollment (STE) ratio will be defined and calculated as the proportion of people who consented to those for whom screening was attempted. Adherence to several aspects (session attendance, dietary, physical activity and self-weights) of the intervention will be tracked to calculate total counts of increase or decrease in adherence. Treatment fidelity will be summarized as an average of the proportion of treatment elements delivered correctly.

To assess the secondary objective, we will examine summary statistics, histograms, and scatter plots of the measured covariates and outcomes for outliers and data trends.

## 10.2 Duration of Response

Duration of overall response: 24 weeks

Duration of stable disease: Stable disease is measured from the start of the treatment until the criteria for progression are met, taking as reference the smallest measurements recorded since the treatment started.

## 10.3 Progression-Free Survival

**Not Applicable**

## 10.4 Other Response Parameters

**Not applicable**

# 11. Data Reporting / Regulatory Considerations

## 11.1 Data Collection

The data collection plan for this study is to utilize REDCap to capture all treatment, toxicity, efficacy, and adverse event data for all enrolled subjects.

### **11.1.1 REDCap**

REDCap (Research Electronic Data Capture) is a free data management software system that is fully supported by the Weill-Cornell Medical Center CTSC. It is a tool for the creation of customized, secure data management systems that include Web-based data-entry forms, reporting tools, and a full array of security features including user and group based privileges, authentication using institution LDAP system, with a full audit trail of data manipulation and export procedures. REDCap is maintained on CTSC-owned servers that are backed up nightly and support encrypted (SSL-based) connections. Nationally, the software is developed, enhanced and supported through a multi-institutional consortium led by the Vanderbilt University CTSA.

## 11.2 Regulatory Considerations

### **11.2.1 Institutional Review Board/Ethics Committee Approval**

As required by local regulations, the Investigator will ensure all legal aspects are covered, and approval of the appropriate regulatory bodies obtained, before study initiation.

Before initiation of the study at each study center, the protocol, the ICF, other written material given to the patients, and any other relevant study documentation will be submitted to the appropriate Ethics Committee. Written approval of the study and all relevant study information must be obtained before the study center can be initiated or the IP is released to the Investigator. Any necessary extensions or renewals of IRB approval must be obtained for changes to the study, such as amendments to the protocol, the ICF, or other study documentation. The written approval of the IRB together with the approved ICF must be filed in the study files.

The Investigator will report promptly to the IRB any new information that may adversely affect the safety of the patients or the conduct of the study. The Investigator will submit written summaries of the study status to the IRB as required. On completion of the study, the IRB will be notified that the study has ended.

All agreed protocol amendments will be clearly recorded on a protocol amendment form and will be signed and dated by the original protocol approving signatories. All protocol amendments will be submitted to the relevant institutional IRB for approval before implementation, as required by local regulations. The only exception will be when the amendment is necessary to eliminate an immediate hazard to the trial participants. In this case, the necessary action will be taken first, with the relevant protocol amendment following shortly thereafter.

Once protocol amendments or consent form modifications are implemented at the lead site, Weill Cornell Medicine, updated documents will be provided to participating sites, as applicable. Weill Cornell Medicine must approve all consent form changes prior to local IRB submission.

Relevant study documentation will be submitted to the regulatory authorities of the participating countries, according to local/national requirements, for review and approval before the beginning of the study. On completion of the study, the regulatory authorities will be notified that the study has ended.

### **11.2.2 Ethical Conduct of the Study**

The Investigators and all parties involved should conduct this study in adherence to the ethical principles based on the Declaration of Helsinki, GCP, ICH guidelines and the applicable national and local laws and regulatory requirements.

This study will be conducted under a protocol reviewed and approved by the applicable ethics committees and investigations will be undertaken by scientifically and medically qualified persons, where the benefits of the study are in proportion to the risks.

### **11.2.3 Informed Consent**

The investigator or qualified designee must obtain documented consent according to ICH-GCP and local regulations, as applicable, from each potential subject or each subject’s legally authorized representative prior to participating in the research study. Subjects who agree to participate will sign the approved informed consent form and will be provided a copy of the signed document.

The initial ICF, any subsequent revised written ICF and any written information provided to the subject must approved by IRB prior to use. The ICF will adhere to IRB requirements, applicable laws and regulations.

### **11.2.4 Compliance with Trial Registration and Results Posting Requirements**

Under the terms of the Food and Drug Administration Modernization Act (FDAMA) and the Food and Drug Administration Amendments Act (FDAAA), the Sponsor-Investigator of the trial is solely responsible for determining whether the trial and its results are subject to the requirements for submission to <http://www.clinicaltrials.gov>. Information posted will allow subjects to identify potentially appropriate trials for their disease conditions and pursue participation by calling a central contact number for further information on appropriate trial locations and trial site contact information.

### **11.2.5 Record Retention**

Essential documents are those documents that individually and collectively permit evaluation of the study and quality of the data produced.  After completion of the study, all documents and data relating to the study will be kept in an orderly manner by the Investigator in a secure study file.  Essential documents should be retained for 2 years after the final marketing approval in an ICH region or for at least 2 years since the discontinuation of clinical development of the IP. In addition, all subjects medical records and other source documentation will be kept for the maximum time permitted by the hospital, institution, or medical practice. 

12. Statistical Considerations

## 12.1 Study Design/Endpoints

This randomized controlled trial will use the following primary endpoints as the promising range to justify further testing of this agent:

- At least 75% attendance rate for the participant and their network members in their respective behavioral coaching sessions.
- 80% of participants or more to have at least one network member engage in the study.
- 85% of participants and their network members or more to complete the final study assessment.

## 12.2 Sample Size/Accrual Rate

The anticipated accrual rate is 8 participants per month (6% of target enrollment).

